#### Secondary objectives

*Aim 2*: To describe the evolution of maternal mental health (ie, anxiety, depression and psychological adjustment scores), from the antenatal period to the neonatal postoperative period (after cardiac surgery), and finally when the child with CHD turns 1 year. We predict that maternal psychological distress will decrease over time, as we expect that the most acute period of stress will be closest to the initial diagnosis of fetal CHD (T1, T2 and T3).

*Aim 3*: To identify the medical and sociodemographic factors associated with prenatal maternal psychological distress of women carrying a fetus diagnosed with cyanotic CHD. We hypothesise that lower maternal educational attainment and poor family support as well as fetal factors such as diagnosis of severe CHD (ie, univentricular heart) will be associated with worse prenatal maternal mental health outcomes (ie, overall mental health, anxiety and depression symptoms). The evaluation of scores obtained on self-report questionnaires (SCL-90-R,^29^ State-Trait Anxiety Inventory (STAI-Y),^31^ Coping Inventory for Stressful Situations (CISS),^32^ Edinburgh Postnatal Depression Scale (EPDS),^33 34^ Posttraumatic Stress Disorder Checklist for DSM-5 (PCL-5)^35 36^) completed by the mother will be analysed in relation to medical, sociodemographic and lifestyle factors.

*Aim 4*: To explore the mediating role of prenatal risk factors (ie, medical factors and maternal coping strategies, such as task-oriented, avoidant and emotional coping) in the association of prenatal maternal mental health (ie, distress, anxiety and depression) and neurodevelopment in children with CHD. We will also explore the potential interaction effects between sociodemographic factors and mental health on neurodevelopment in CHD. We hypothesise that expecting mothers with low socioeconomic levels of support and/or with maladaptive coping strategies (eg, avoidant, emotional reactivity) will experience the greatest effects of prenatal distress on their children’s neurodevelopmental outcomes at 1 year of age. The mediating role of medical and psychological antenatal factors (information extracted from the medical record, the interview and the information questionnaire) on the relationship between maternal mental health scores (SCL-90-R, STAI-Y, CISS, EDPS, PCL-5) and the child’s neurodevelopment (Bayley-4,^30^ Ages and Stages Questionnaire-Third Edition (ASQ-3)^37^) will be characterised.

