#### Secondary objectives

##### Aims 2 and 3

In order to study changes over time (ie, evolution of maternal mental health) in the scores obtained on the self-report questionnaires (SCL-90-R, STAI-Y, CISS, PCL-5, EPDS) completed by the mother and to study changes as a function of medical, sociodemographic and lifestyle factors, a linear mixed model will be applied. This model takes into account the random effect induced by the analysis of three repeated measurements. The cofactors tested (fixed effects) will be the variables likely to influence the scores on these self-report questionnaires (medical, sociodemographic and lifestyle). The results of the linear mixed model are expressed for each factor in the form of a coefficient corresponding to the variation brought about by this factor on the basal score (intercept). A positive coefficient indicates a score-raising effect, while a negative coefficient indicates a score-lowering effect. For the time effect, the coefficient reflects the variation during the follow-up, while for the other factors, the estimate reflects the variation induced by the presence of the factor. The interactions between the co-factors and time will also be tested. A similar methodology will be applied for each score.

##### Aim 4

We will use a structural equation model to estimate simultaneously the relationships among maternal mental health (as captured by SCL-90-R, STAI-Y, CISS, PCL-5 and EPDS scores), prenatal factors (medical, sociodemographic and psychological) and child development (Bayley-4 and ASQ-3).

The structural pathways linking these three latent constructs, whereby maternal mental health impacts prenatal factors, which in turn influence the child’s development, while also allowing for a residual direct effect of maternal mental health on developmental outcomes.

We will quantify the mediating role of each block of prenatal factors by estimating the proportion of the effect of maternal mental health on child development that is transmitted through those factors. The model will be fitted using robust maximum likelihood estimation, with bootstrapping to derive CIs for indirect effects.

##### Aim 5

The GSI of the SCL-90-R will be used as an indicator of co-parent mental health. It is a standardised score with a T-score (mean 50, SD 10). The Bayley-4 cognitive score will be used as an indicator of neurodevelopment in children with CHD at age 1. This is an exploratory analysis, independent of the primary outcome.

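### Aim 4 hypothesises that distress does more harm in some mothers than in others, but its stated analysis is a mediation model with no interaction on the child's outcome

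*Protocol article*

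**What the plan says.** All references are to the Protocol article.

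**Aims and hypotheses, Secondary objectives, Aim 4** makes three statements:
- The aim is mediation: "To explore the mediating role of prenatal risk factors (ie, medical factors and maternal coping strategies" are to be studied as intermediates between maternal mental health and neurodevelopment.
- An interaction is announced for sociodemographic factors: "We will also explore the potential interaction effects between sociodemographic factors and mental health on neurodevelopment in CHD".
- The hypothesis concerns which mothers are most affected. Those with low socioeconomic support and/or "with maladaptive coping strategies (eg, avoidant, emotional reactivity) will experience the greatest effects of prenatal distress on their children’s neurodevelopmental outcomes".

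**Data analysis plan, Secondary objectives, Aim 4** fixes one model, an SEM with three constructs:
- The exposure is "maternal mental health (as captured by SCL-90-R, STAI-Y, CISS, PCL-5 and EPDS scores".
- The prenatal factors are medical, sociodemographic and psychological.
- The outcome is child development on Bayley-4 and ASQ-3.
- The paths are those "whereby maternal mental health impacts prenatal factors, which in turn influence the child’s development, while also allowing for a residual direct effect".
- The outputs are bootstrap intervals for indirect effects and a proportion mediated for each block: "We will quantify the mediating role of each block of prenatal factors by estimating the proportion of the effect of maternal mental health".

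The only interaction named in the Data analysis plan belongs to Aims 2 and 3, where the outcome is the mother's own score: "The interactions between the co-factors and time will also be tested". The Main objective regression names none.

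**The concern.** A hypothesis about who suffers the greatest effect says that the slope of the child's score on maternal distress changes with coping or support. A mediation model asks something else: how much of one common slope passes through an intermediate variable. The stated Aim 4 analysis answers only the second question.

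The roles of the variables are also inconsistent. Coping is a mediator in the aim, a moderator in the hypothesis, and part of the exposure in the SEM. Sociodemographic factors are moderators in the hypothesis and in the announced interaction, but the SEM places them downstream of maternal mental health, as things that distress influences.

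If the plan is followed as written, true effect modification by coping would go unexamined, and the hypothesis could be neither supported nor refuted by the analysis listed under it.

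**Working it through.** **1. The roles side by side**

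| Factor | Aim | Hypothesis | SEM |
|---|---|---|---|
| Coping (CISS) | Mediator | Moderator | Listed with the exposure measures |
| Sociodemographic / support | Interaction announced | Moderator | In the mediator block |
| Interaction on child outcome | Sociodemographic only | Implied for both | None |

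**2. Why the SEM outputs cannot answer the hypothesis**

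Let x be distress, m the third variable and y the child's score.
- Mediation: m = a·x + error and y = c·x + b·m + error. The effect of x on y is c + a·b, and the proportion mediated is a·b / (c + a·b). Both are single numbers, the same for every mother.
- Moderation: y = β1·x + β2·m + β3·x·m + error. The slope of y on x is β1 + β3·m. The hypothesis is a statement about β3, which does not appear in the mediation model.

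**3. Size of the contrast (illustration with assumed effects)**

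The documents give no interaction or path sizes, so these are assumptions: 70 dyads, standardised x and m, main effect of x = -0.3, residual SD 0.85, two-sided 5%. The indirect effect is tested by joint significance of its two paths, with 3,000-4,000 runs per scenario.

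| Scenario | Indirect effect significant | Product term significant |
|---|---|---|
| Moderation only (-0.3 per SD x SD; m unrelated to x and without a main effect) | 0.3% | about 75% |
| Mediation only (both paths 0.4 in size) | 88-89% | about 4% |

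The 4% is the nominal error rate, so the two tests can point in opposite directions on the same data.

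**4. Precision available for an interaction**

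- The plan's sample size, from Sample size and power considerations: testing 10 covariates jointly with an R² increase of 0.20 over a predictor with R² = 0.45² = 0.2025 gives f² = 0.20 / (1 - 0.4025) = 0.335, noncentrality 0.335 × 72 = 24.1 on (10, 60) df, and power 0.905. This reproduces 72. The total follows as 72 × 1.2 = 86.4, rounded up to 87. After 20% attrition, 87 × 0.8 = 69.6, about 70 dyads. Neither figure was sized for an interaction.
- The 75% above is for a bare model with x, m and their product. With 10 covariates of no effect added, it falls to 69%. With three product terms as well, it is about 65-67% for an interaction of 0.3, 38% for 0.2 and 13% for 0.1.
- As shares of outcome variance (x² coefficient 0.09, residual 0.85² = 0.7225): 0.3 gives 0.09 / (0.09 + 0.09 + 0.7225) = 10%; 0.2 gives 0.04 / (0.09 + 0.04 + 0.7225) = 4.7%; 0.1 gives 0.01 / (0.09 + 0.01 + 0.7225) = 1.2%.
- Noncentral F cross-check: one interaction added to 11 main effects, 72 dyads, assumed base R² of 0.20 to 0.40. The smallest R² increment detectable at 80% power is about 0.06 to 0.08. Power is 58-71% for an increment of 0.05 and 27-34% for 0.02.

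**The case against.** The strongest reply is that this is a condensed article describing an exploratory secondary aim, whose full analysis plan is not shown. The aims do announce a sociodemographic interaction on neurodevelopment, and Covariate measures says that socioeconomic vulnerability indices will enter exploratory socioeconomic analyses. The exact model term could be left to the full plan.

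That stands in part. A reader might infer that the whole hypothesis is never tested; the documents do not support this for the socioeconomic half, where the interaction is announced and only its place in the analysis is missing. It does not rescue coping: no coping interaction is announced in the aims or the analysis. Nor is this simple silence. The Aim 4 analysis is fixed down to estimator, bootstrap and summary measure, and it assigns both factors to roles that conflict with the hypothesis.

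A reader might also infer that the mediation result will be presented as the answer to which mothers are most affected. The article does not say so. It labels the output as mediation, and the Discussion links preventive targeting to the study's data in general. This is a risk to guard against, not a stated intention.

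Finally, the simulation rests on chosen effect sizes and shows a general property of the two analyses, not a result about this study. The 75% in particular should not be taken as the power of a realistic model with covariates.

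**Conclusion.** The point holds. The Aim 4 hypothesis is effect modification by socioeconomic support and coping, and the Aim 4 analysis contains no interaction for either. Its indirect effects and proportions mediated cannot show whether the distress slope differs between mothers. For coping the mismatch is complete and is compounded by CISS being listed with the exposure measures. For sociodemographic factors it is a failure to carry an announced interaction into the analysis.

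This follows from the text alone and needs no assumed numbers. The power figures do rest on assumptions: independent normal variables, a residual SD of 0.85, covariates without effect and about 70 evaluable dyads. The primary analysis is not affected. The matter is worth correcting because a stated hypothesis has no matching analysis and the correction is cheap.

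**What to change.** Reconcile the Aim 4 text in Aims and hypotheses with the Aim 4 text in the Data analysis plan:

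1. Add a separate exploratory regression of the Bayley-4 cognitive score. Include the main effects and the products of centred T1 GSI with CISS emotion-oriented coping, with CISS avoidance-oriented coping, and with the socioeconomic vulnerability or support measure. Name that measure, since the article describes vulnerability indices and separate support items rather than one index.
2. Leave the Main objective regression unchanged. Product terms placed there would make the primary GSI coefficient conditional on the moderator values.
3. Report the distress slope with a 95% CI at low and high values of each moderator, labelled exploratory.
4. Give CISS one stated role in the SEM, and state that the proportion mediated does not address which mothers are most affected.

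If moderation is not intended, rewording the hypothesis as mediation and dropping the interaction sentence would also remove the conflict. A multi-group or latent-interaction SEM is another route to the same test.

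**Cost:** analysis wording and one extra model. GSI, CISS and the sociodemographic questionnaire are already collected from the mother at T1 (Procedures). The downside is limited precision: a null interaction would not rule out moderate effect modification, so the intervals matter more than the p values.

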## DISCUSSION

This article presents the background and design of the first multicentre longitudinal study investigating the impact of prenatal maternal mental health on 1-year neurodevelopmental outcomes in children with CHD who undergo neonatal open-heart surgery (ie, children at higher neurodevelopmental risk). The risk of deterioration in maternal mental health is particularly high in the case of a complex cyanotic CHD diagnosis in the infant. We will evaluate maternal mental health at three time points, and its effect on the neurodevelopment in the child with CHD.

Our study is the first research initiative to investigate the link between prenatal parental mental health and neurodevelopmental outcomes in children with complex cyanotic CHD at age 1. Understanding the risk factors for neurodevelopmental impairments, from the prenatal period onwards, is a public health priority. A multifaceted approach including psychological modifiable factors is needed to improve these impairments. The psychological data collected in this study are necessary for better anticipating preventive strategies for this high-risk population, particularly by enhancing our knowledge about the critical effects of prenatal maternal stress on children’s neurodevelopment. It thus will enable us to better target preventive strategies for the psychological well-being of families, involving adapted prevention protocols in fetal and congenital cardiology units for parents whose child is diagnosed with complex cyanotic CHD. We anticipate that long-term follow-up of this cohort is needed to better characterise the potential long-lasting effects of prenatal parental stress on neuropsychological development in children with CHD. Ultimately, our overarching goal is to propose interventions to improve maternal mental health, as a potentially modifiable protective factor that can mitigate or prevent neurodevelopmental impairments in youth with CHD.

### Ethics and dissemination

This study is sponsored by the French National Institute of Health and Medical Research. It was granted approval by local Ethics Committee ‘Comité de Protection des Personnes Ouest IV’ (file number 2024-A02138-39) on 5 November 2024 and is registered in a public trials registry (NCT06711666). The Neuro-Moms CHD project targets a critical public health question regarding maternal mental healthcare for children with chronic diseases. Heart disease being the first cause of congenital anomalies, the societal implications are expected to be broadly communicated not only within the scientific community but also the lay public. After final analysis, the results will be published in the form of scientific articles in peer-reviewed journals and presented at national and international conferences. Any publication or communication (oral or written) will be decided by mutual agreement between the co-ordinating and PIs, the scientific managers and the sponsor, and will comply with the international recommendations: ‘Recommendations for the Conduct, Reporting, Editing, and Publication of Scholarly work in Medical Journals’ (http://www.icmje.org/recommendations). All parents/guardians and children will give written informed consent or assent to participate prior to entering the study.

### Study progress

The study will start in June 2025. This is Protocol V.1.0, 24 September 2024. Potential protocol amendments will be communicated and updated in clinicaltrials. gov. https://clinicaltrials.gov/study/NCT06711666?id=NCT06711666&rank=1.
